**Trial Personnel:**

Facilitators will be responsible for conducting weekly DWM sessions with participants, via Zoom or phone calls. Facilitators are bilingual (English/Farsi) speakers with prior experience working with people from refugee backgrounds in Indonesia (e.g., previously working as teachers at refugee learning centers, staff in refugee-led originisations and/or interpreters for refugee-focused NGOs in Indonesia). Facilitators will receive 28 hours of in-person training by the research team. The in-person training covers: the DWM manual and techniques, general counselling/facilitation techniques, and responding to participant distress. Ongoing monitoring of facilitators’ capacity to practice will be conducted through regular supervision by a member of the research team who is a Clinical Psychologist. This oversight will help to ensure that any potential concerns about the capacity of the facilitators to carry out their roles is identified and addressed. Protocol adherence will be ensured by regular supervision of the facilitators and treatment fidelity checks using a checklist.

Assessors will be responsible for conducting the Structured Assessments with participants, via Zoom or phone calls. Assessors are bilingual (English/Farsi) speakers with prior experience working with people from refugee backgrounds in Indonesian (e.g., previously working as teachers at refugee learning centers, staff in refugee-led organisations and/or interpreters for refugee-focused NGOs in Indonesia). Assessors will receive 28 hours of in-person training by the research team. The in-person training covers: administering the instruments, general interview techniques, and responding to participant distress. Ongoing monitoring of assessors’ capacity to practice will be conducted through regular supervision by a member of the research team who is a Clinical Psychologist. This oversight will help to ensure that any potential concerns about the capacity of the assessors to carry out their roles is identified and addressed. Protocol adherence will be ensured by regular assessment fidelity checks using a checklist.

Supervisors are responsible for supervising the facilitators and assessors in the day-to-day running of the trial. Supervisors will hold at least Masters-level qualifications in Clinical Psychology.

**Trial Treatment:**

The active treatment is the DWM intervention (see Section 10. Treatment of Subjects for a summary of this intervention and its modules). Participants in the Active Treatment condition will receive the guided version of DWM. This involves receiving the DWM workbook, audio files, and five weekly facilitator calls. Participants in the Waitlist Control condition will gain access to the DWM workbook and audio files upon the completion of their study participation (i.e., following the completion of the final assessment in week 9).

**Measurement Instruments:**

The instruments used to assess and monitor mental health and psychosocial functioning are outlined in the below table.

|  | **When measure is administered** | | | | |
| --- | --- | --- | --- | --- | --- |
| **Construct & Measure** | **Screener** | **Structured Assessment 1** | **Structured Assessments 2-4** | **Ecological Momentary Assessment** | **DWM sessions** |
| Demographics | X | X |  |  |  |
| Psychological Distress (K10)* | X | X | X |  |  |
| Posttraumatic Stress Reactions (PCL-6) |  | X | X |  |  |
| Suicidal Ideation (SIDAS) |  | X | X |  |  |
| Self-Identified Problems (PSYCHLOPS) |  | X | X |  |  |
| Wellbeing (WHO-5) |  | X | X |  |  |
| Psychological Flexibility (adapted CompACT & AAQ-II) |  | X | X |  |  |
| Repetitive Negative Thinking (PTQ- Short form) |  | X | X |  |  |
| Intolerance of Uncertainty (abbreviated IoUS) |  | X | X |  |  |
| Social Satisfaction and Functioning (abbreviated WHOQoL-BREF items and SAS-SR-modified) |  | X | X |  |  |
| Physical Health (abbreviated WHOQoL-BREF) |  | X | X |  |  |
| Post-Migration Living Difficulties (adapted PMLD Checklist) |  | X | X |  |  |
| Perceived benefit (newly adapted items) |  |  |  | X |  |
| Adverse Life Events (adapted HTQ) |  | X |  |  |  |
| Digital Markers** |  | X | X |  |  |
| Momentary Emotions and Stressors |  |  |  | X |  |
| Emotion Regulation Strategies (RESS-EMA) |  |  |  | X |  |
| Treatment fidelity (checklists) |  |  |  |  | X |
| Treatment contamination check |  | X | X | X |  |

*Psychological Distress (K10) is the primary outcome measure

**Digital Markers are measured in Structured Assessments 1 and 3 only.

*Screener and Primary Outcome Measure*

*Psychological Distress*

Psychological distress will be measured through the Kessler-10 Psychological Distress Scale (Kessler et al., 2002). Ten items related to distress are rated on a five-point Likert scale. The sum of the ten items gives a total score ranging from 10 to 50. In a study among Kurdish and Afghan (former) refugees and asylum seekers in New Zealand and Australia, the following cut-off scores were used: 10-15.9 (*low risk of psychological distress*), 16-21.9 (*moderate levels of distress consistent with a diagnosis of moderate depression and/or anxiety disorder*), 22-29.9 (*high level of distress*) and 30 or more (*possibility of very high or severe levels of distress*) (Sulaiman-Hill & Thompson, 2010). In the current study, we will use a score of >19.9 as an indication of moderate to high levels of psychological distress. The K10 was found to be an accurate screener for common mental disorders cross-culturally (Patel et al., 2008; Fassaert et al., 2009, Sulaiman-Hill & Thompson, 2010, Tol et al., 2020). Furthermore, the K10 strongly correlated with other validated measures for screening for common mental disorders in primary care patients in India (*r*=.68 with GHQ-12 and *r*=.84 with SRQ, respectively) (Patel et al., 2008).

*Secondary Outcome Measures*

*PTSD symptoms*

Posttraumatic stress disorder (PTSD) symptoms during the past week according to a DSM-5 PTSD diagnosis will be measured using the PTSD Checklist for DSM-5, 6-item version (Weathers et al., 2013). Items are rated on a 0-4 scale and are summed to calculate a total severity score, with higher scores indicating worse symptomatology. This measure has previously been used with refugees (Tol et al., 2020).

*Suicidal Ideation*

The Suicidal Ideation Attributes Scale (SIDAS; Van Spijker et al., 2014) will be used to measure the presence and inference of suicidal thoughts over the past week. The scale has 5 items, each rated on a 0-10 scale. Scores are summed to calculate a total severity score, with high scores indicating worse symptomatology. However, if a participant scores zero on the first item, then items 2-4 are not administered.

*Self-identified Problems*

The Psychological Outcomes Profiles (PSYCHLOPS) scale is a patient-generated outcome measure as an indicator of change after therapy (Ashworth et al., 2004). PSYCHLOPS consists of four questions. It contains three domains: problems (2 questions), function (1 question), and wellbeing (1 question). This trial will use the ‘problems’ questions only, as functioning and wellbeing will be measured by other instruments in the assessment battery. Participants are asked to give free text responses to the problem domains. Responses are scored on an ordinal six-point scale. PSYCHLOPS has been validated in primary care populations across several countries (Czachowski, Seed, Schofield, & Ashworth, 2011; Héðinsson, Kristjánsdóttir, Ólason, & Sigurðsson, 2013).

*Wellbeing*

Wellbeing and quality of life over the past week will be measured using the World Health Organisations Wellbeing Index (WHO-5; Topp et al., 2015). The scale comprises 5 items, scored on a 0-5 scale, where higher scores indicate greater wellbeing. Items are summed to create a total score. The measure has previously been used in with refugees (Tol et al., 2020).

*Functional Impairment*

Data on health and functional disability will be collected using the 12-item WHO Disability Assessment Schedule 2.0 (WHODAS 2.0) (WHO, 2010b). The WHODAS assess levels of functional impairement resulting from any disease(s), including mental neurological and substance use disorders. It is simple to administer and applicable across cultures and can be used in all adult populations. The WHODAS covers six domains (cognition, mobility, self-care, getting along, life activities, participation). Difficulties are scored on a five-point Likert scale ranging from 0 (none) to 4 (extreme), before summation (range 0-48). Higher scores indicate worse functional impairment. We will use the 12-item interviewer administered version, which has been validated in different cultural contexts (WHO, 2010a).

*Digital Markers*

Data on facial and vocal markers of positive and negative affect and arousal will be collected digitally, using participants responses to two standardised prompts (Schultebraucks et al., 2022; Meaney et al., Under Review). Following the administration of the PSYCHLOPS (standardised outcome measure noted above), where each participant identified the most salient current problem in their life, participants will be asked to describe this problem and their emotional responses for one minute. Following this, participants will then be asked to describe a salient positive experience, event or relationship and their emotional responses for one minute. The one-minute recordings will be extracted from the Structured Assessment zoom recording for analysis of facial (e.g., expressivity), acoustic (e.g., volume, frequency, amount of speech), speech content (e.g., sentiment) and head movement. Digital measurement of facial and vocal markers of negative affect and arousal have been validated to investigate indices relating to negative affect, arousal and emotion regulation (Meaney et al., Under Review). Further, this integrated form of assessment (that makes use of existing assessment recordings) significantly reduces participant burden. This approach is routinely used with clinical populations, including individuals experiencing severe depression (Abbas et al., 2021), schizophrenia (Abbas et al., 2021; 2022), PTSD (Meaney et al., Under Review) and suicide (Galatzer-Levy et al., 2021).

Hypothesised Mechanisms

*Psychological Flexibility*

The Comprehensive assessment of Acceptance and Commitment Therapy processes (CompACT; Golijani-Moghaddam et al., 2023) will be used to measure the presence of psychological flexibly over the past week. An adapted version of the scale, comprising 10 items, will be administered. Items are scored on a 7-point scale, with some reverse scored items. Items are summed to create three subscale scores indexing: openness to experience, valued action and behavioural awareness. Higher scores indicate higher levels of psychological flexibility in each domain.

Acceptance and Action Questionnaire-II (Hayes et al., 2004) will be used to assess psychological inflexibility over the past week. The scale comprises 7 items (on a 7-point Likert scale). Higher scores indicate higher levels of psychological inflexibility characterized by greater experiential avoidance. This scale has been extensively used in the literature, including randomized controlled trials with forcibly displaced people (Acarturk et al. 2022; Lakin et al., 2023). The psychometric properties of the scale were reported excellent (Ong et al., 2024).

*Emotion Regulation*

In the current study, emotion regulation will be assessed using an ecological momentary assessment (EMA) paradigm, which will involve two 1-week EMA blocks (each comprising 5 ultra-brief surveys per day for 7 days). Each survey will comprise 21 items in total: nine items assessing momentary emotional states (e.g., anger, sadness, relaxation; adapted from Cloos, Ceuleman & Kuppens., 2023), eight items assessing momentary emotion regulation strategy use (e.g., rumination, suppression, acceptance; adapted from the Regulation of Emotion Systems Survey-EMA version; Medland et al., 2020), and 4 items assessing momentary stressors (e.g., positive event, negative event, event unpleasantness/pleasantness; adapted from Baik & Newman, 2023). Items are scored on a 0-100 sliding scale. An EMA paradigm, using similar items, have been employed with refugees (Koch et al., 2020).

*Repetitive Negative Thinking*

The short form of the Perseverative Thinking Questionnaire (PTQ) (Ehring et al., 2011) will be used to measure to which extent participants are impacted by negative repetitive thinking over their problems on a 5-point Likert Scale (0 = Never, 4 = Almost Always). The short form (Moeller et al., 2023) consists of 9 items tapping into three subscales: core feature and unproductiveness of repetitive negative thinking, and mental capacity captured by it. Higher scores indicate higher levels of repetitive negative thinking. The scale has previously been used in several studies, including randomized controlled trials with trauma-exposed populations (Heckendorf et al., 2019).

*Intolerance of Uncertainty*

The Intolerance of Uncertainty Scale-short version (Carleton et al., 2007) will be used to measure the presence of intolerance of uncertainty. The current study will use an abbreviated version of the scale, comprising 6 items rated on a 1-5 scale, to reduce the administration burden on the participant. Items are summed to create two subscale scores indexing: prospective anxiety and inhibitory anxiety. Higher scores indicate higher levels of intolerance for uncertainty in each domain. This scale has previously been used with refugees (Nickerson et al., 2019).

*Social Satisfaction and Functioning*

Social satisfaction over the past week will be measured using two items from the World Health Organisation’s Quality of Life Scale (Brief Version) (WHOQoL-BREF; WHO, 1998). Items are scored on a 1-5 scale, where higher scores indicate greater social satisfaction. This scale has previously been used with refugees (Tissue et al., 2022). The modified version of the Social Adjustment Scale-Self Report (SAS-SR) (Cooper et al., 1982; Weissman & Bothwell, 1976) will be used to assess participants’ social functioning with 9 items rated on a 5-point Likert Scale (1 = Not at all, 5 = All the time). Higher scores indicate higher social functioning over the past 7 days. The scale has been widely used with trauma-exposed populations in a range of studies, including RCTs (Scoglio et al., 2020).

Covariates

*Physical Health*

Physical health over the past week will be measured using two items from the World Health Organisation’s Quality of Life Scale (Brief Version) (WHOQoL-BREF; WHO, 1998). Items are scored on a 1-5 scale, where higher scores indicate better physical health. This scale has previously been used with refugees (Tissue et al., 2022).

*Post-Migration Living Difficulties*

Post-migration stressors will be assessed using a version of the Post-Migration Living Difficulties Checklist (PMLDC) (Silove, Sinnerbrink, Field, Manicavasagar, & Steel, 1997; Steel, Silove, Bird, McGorry, & Mohan, 1999) adapted to the Swiss context. This 17-item scale examines the extent to which post-migration challenges had been of concern to the individual over the past 12 months. Items are rated on a five-point scale, ranging from 0 (*not a problem*) to 4 (*a very serious problem*). Items scored at least 3 (*a serious problem*) are considered positive responses, yielding a total count of living difficulties. This scale has consistently been identified as a predictor of mental health among displaced populations (Nickerson, Bryant, Steel, Silove, & Brooks, 2010; Schweitzer et al., 2006; Steel et al., 2006) and has previously been used with Farsi speaking refugees (Nickerson et al., 2015; Schick et al., 2016). In the current research, we will assess post-migration challenges over the past week and the period since the last assessment (at post-intervention assessment and follow-up).

*Exposure to Adverse Life Events*

Exposure to traumatic events will be assessed using an adapted version of the Harvard Trauma Questionnaire (Mollica et al., 1992). The HTQ measures exposure to different types of adverse life events, such as forced isolation, serious injury and war-related combat, using a 16-item checklist. A total count of the types of adverse life events that each individual had experienced and/or witnessed will be derived. In the current research, an adapted version of the scale (that combines similar items to create 8 items overall) will be used to reduce administration burden for the participant.

Other Measures

*Treatment Contamination Check*

Lifetime and current access to mental health services will be measured using a context-adapted item from the Access to Health Care Services questionnaire developed by the STRENGTHS project (Fuhr et al., 2020). Also, participants will be asked to indicate if they gained informal access to the active intervention materials (DWM workbook or audio files) before starting the trial or while undergoing the WL period in the trial. These questions will be in self-report format (rather than interview format), administered at the conclusion of the final EMA survey block, to reduce demand characteristics.

*Perceived Benefit*

Participants’ subjective perception of whether participation in the study led to any direct benefits (i.e., psychological, social or economic benefit) will be assessed using brief self-report questions developed for this project. These questions will be in self-report format (rather than interview format), administered at the conclusion of the final EMA survey block, to reduce demand characteristics.

# **Safety and Monitoring**

1. Assessment of Safety Event Report Forms

Safety reports will be assessed on the seriousness, causality, and expectedness of the event to the trial treatment(s), intervention(s), investigational medical product(s), investigational medical device(s). The following are known and expected adverse effects, harms, risks or discomforts associated with trial procedures, treatments or interventions.

1. Known Adverse Effects

There are no known adverse effects associated with this intervention. The DWM intervention is low-intensity and implements present-focused psychological strategies that have been demonstrated to improve mental health. Thus, we do not anticipate any additional risk or burden for participants.

1. Known Harms, Risks or Discomforts

Participants will be asked to respond to interview questions, and complete brief online questions, about their psychological state and mood, physical health, refugee status and their history of stressful events. This procedure may lead to transient psychological distress, however no psychological stress will be placed on participants that they do not normally experience. Administering the instruments is crucial to draw conclusions about the intervention’s efficacy and mechanisms of change. The research team has extensive experience in conducting research with refugees in Indonesia and Australia and the project Assessors have been trained in interview techniques and how to manage negative emotional reactions in participants.

Participants will be in regular contact with the research team throughout the intervention (with Structured Assessments every 3-weeks and regular facilitator calls during the DWM phase). If, at any stage, the participant experiences an undesirable emotional reaction or indicates they are experiencing significant symptoms (i.e., issues in line with our exclusion criteria, such as symptoms consistent with a severe physical or mental condition) then the trained assessor/facilitator will be able to triage the issue by either

(1) providing referral information directly to the participant so they can access more specialised services, or

(2) escalating the participant to the research team's clinical supervisor who can assess and refer as needed.

1. Adverse Events or Adverse Reactions

Adverse events (AE) are considered any untoward medical occurrence in a patient or clinical trial participant administered the intervention, which does not necessarily have a causal relationship with this treatment.

Adverse Reactions (AR) are considered untoward and unintended responses to the trial intervention related to any intervention procedures.

AEs and ARs are assessed using the safety monitoring flow chart. Those classified as "not serious" are assessed by the qualified physician/medical expert specified in section 2 of the protocol. The Qualified Physician cannot delegate this responsibility to other research personnel.

Adverse event reports must be reported to the Coordinating Principal Investigator without undue delay. All adverse event reports must be recorded in the [UNSW Safety Monitoring Register Template](https://research.unsw.edu.au/document/UNSW%20Safety%20Monitoring%20Register%20Template.xlsx).

1. Serious Adverse Events

Serious Adverse Events (SAEs) that result in or lead to one or more of the following and the event is not related to the trial intervention:

- The death of a trial participant.
- A life-threatening illness or injury involving a trial participant.
- A participant's permanent impairment of body structure or body function.
- In-patient or prolonged hospitalisation (not for a pre-existing condition or an elective surgery) of a trial participant.
- Medical or surgical intervention to prevent life-threatening illness or injury or permanent impairment to a body structure or function of a trial participant.
- Fetal distress, fetal death or congenital abnormality or birth defect.

SAE reports are classified following the safety assessment flowchart and are assessed by Sponsors Independent Medical specified in section 2 of the protocol. The Sponsors Independent Medical cannot delegate this responsibility to other research personnel. SAE reports are reported to the Coordinating Principal Investigator within 48 hours of the event occurring for multicentre clinical trials. SAR reports must be recorded in the [UNSW Safety Monitoring Register Template](https://research.unsw.edu.au/document/UNSW%20Safety%20Monitoring%20Register%20Template.xlsx).

1. Serious Adverse Reactions

A Serious Adverse Reactions (SAR) is an SAE that is related to the trial intervention. SAR reports are classified following the safety assessment flowchart and are assessed by Sponsors Independent Medical specified in section 2 of the protocol. The sponsors independent medical expert must determine whether the SAR was expected or unexpected. The Sponsors Independent Medical cannot delegate this responsibility to other research personnel.

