# **Treatment** **of Subjects**

The DWM Intervention Program

DWM is a brief, remotely delivered, self-help intervention (see Doing what matters in times of stress: an illustrated guide. Geneva: World Health Organization; 2020 (<https://www.who.int/publications-detail-redirect/9789240003927> ). It is an illustrated guide of an existing intervention called Self-Help Plus (SH+) (Epping-Jordan et al., 2016). The DWM manual was released by the WHO in 2020 to support the remote delivery of SH+, considering the COVID-19 pandemic and a growing need for online/remotely delivered interventions. DWM is:

- based on acceptance and commitment therapy and adapted for many settings;
- intended as an intervention for managing stress and coping with adversity;
- relevant for anyone above the age of 18;
- designed to be completed over a short period of time;
- practical so that participants can practise skills regularly on their own; and
- illustrated, with accompanying audio recordings to support regular practice.

DWM can be delivered as either a guided or unguided intervention. For the current project, we are testing the guided version of DWM. This means that participants in the active treatment condition will receive a copy of the DWM illustrated workbook that contains five ‘lessons’. This workbook will be accompanied by audio files that provide guided scripts for practicing the newly learnt techniques. Finally, participants will also receive five weekly calls from a trained facilitator, who will help participants to learn and practice the therapeutic techniques. This delivery format is empirically supported by meta-analyses on the therapeutic effects of bibliotherapy, prerecorded self-help interventions, and guided self-help interventions (Cuijper, Munoz, Clarke & Lewinson, 2009; Cuijpers, Donker, van Straten & Andersson, 2010). Participants in the waitlist control condition will gain access to the unguided version of DWM (i.e., workbook and audio files) upon completion of their final assessment at the end of the 9-week waitlist period.

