The DWM program is based on Acceptance and Commitment Therapy (ACT; Hayes et al., 2013) techniques that are empirically supported (Hacker, Stone & MacBeth, 2016) and formally recommended by the WHO. The manual involves the following empirically supported elements: psychoeducation, grounding, cognitive defusion, mindfulness exercises, values clarification, and compassion exercises. There is substantial evidence linking ACT-based interventions to reductions in anxiety, depression and stress (Hacker et al., 2016; French, Golijani-Moghaddam & Schroder, 2017).

DWM Skills and Modules

DWM seeks to reduce psychological symptoms by introducing stress management techniques. It comprises five weekly modules, each focused on a specific skill (see Table 1). The specific skill is first learnt via the DWM illustrated workbook and accompanying audio file(s), and then practiced and reinforced by the weekly session with a trained facilitator.

*Table 1. Overview of DWM Modules*

| **Lesson (Overall Theme)** | **Main Goal(s)** | **Core technique(s)** |
| --- | --- | --- |
| 1 (Grounding) | - Practice present-centered awareness during an everyday activity - Practice grounding, to respond effectively to stress | - Psychoeducation - Grounding/Contact with the present moment |
| 2 (Unhooking) | - Practice noticing and naming difficult thoughts and feelings - Refocus on the present | - Grounding/Contact with the present moment - Acceptance - Defusion |
| 3 (Values) | - Identify personal values - Learn to engage in values-guided actions | - Values - Committed Action |
| 4 (Being Kind) | - Enhance kindness to yourself and others | - Compassion towards self and others |
| 5 (Making Room) | - Learn how to accept/tolerate difficult thoughts and feelings via compassion | - Acceptance - Defusion |

The Control Condition

Participants in the Waitlist Control condition will participate in repeated assessments (mid-treatment, post-treatment and follow-up assessments) over a 9-week waitlist period. Following completion of the final assessment, participants will be receive a link to the DWM workbook and audio files.

Use of Co-Intervention (if applicable): Participants are allowed to use any existing prescribed medication or routine care related to any co-morbid health conditions.

- 1. **Trial Intervention**

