Participants deemed eligible based on the online screener and phone screener process will be invited to participate in the trial and sent a link to review the trial’s Participant Information Statement and Consent Form. Following informed consent, participants will be contacted to book their first assessment (Structured Assessment 1). Structured Assessments will be conducted by trained research assistants called ‘Assessors’ (see ‘Trial Personnel’ below) and will involve the administration of the scales in a structured interview format to assess mental health and psychosocial functioning (see ‘Measurement Instruments’ below). If, at the time of the baseline assessment (Structured Assessment 1), the participant’s symptoms of psychological distress have spontaneously improved such that they no longer score above the cut-off, they will be provided feedback on their test outcomes and it will be explained why they are no longer eligible for the study.

After the baseline assessment, participants will be randomized on a 2:1 (active treatment : waitlist control) basis by an independent research assistant, not involved in the assessments, using computerized software. Participants will be randomised to either the Active Treatment condition (*n*=214) or the Waitlist Control condition (*n*=107) to form a single-blind waitlist control RCT design. Participants in the Active Treatment condition will receive the 5-week DWM intervention from Weeks 1-5. Regardless of condition, all participants will complete Structured Assessments every 3 weeks.Upon completion of the final Structured Assessment (1-month follow-up, conducted 9-weeks following baseline assessment), participants in the Waitlist Control condition will gain access to the DWM workbook and audio files.

The instruments administered in Structured Assessments 2-4 closely resemble those used in Structured Assessment 1, with minor changes (as some scales do not need to be re-administered). This is outlined in the ‘Measurement Instruments’ section below. In case participants do not attend a scheduled assessment, the research team will attempt to contact them via follow-up text messages and/or phone calls for a maximum of eight times for scheduling a new appointment.

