#### **Annual assessment of safety**

The following information must be provided in a report to the sponsors delegate annually:

- Documented evidence that the Trial Management Group, Trial Safety Committee, or the Data Safety Monitoring Board (e.g. meeting minutes) confirmed that regular safety reviews occurred.
- Analysis of the trial intervention(s) and its implications for participants considering all available safety data and relevant clinical or non-clinical studies results.
- Any reports of emerging safety issues and a description of any measures taken or proposed to minimise risks.
- A copy of the safety monitoring register.

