- Treatment fidelity: In order to determine whether the intervention-as-implemented does not differ from the intervention-as-designed, fidelity checklists filled out by research assistants independent to the treatment facilitation team will be completed for a random sample, stratified on facilitator, of sessions/participants. Treatment fidelity will be analysed as a manipulation check.

Interim analysis (if applicable): Interim analyses will be considered in case safety issues are (suspected to be) violated.

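### Harms have more scheduled chances of being noticed under DWM than on the waitlist in weeks 1-5, and no adverse-event question is put to both arms on a common schedule

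*Protocol*

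**What the plan says.** In the Safety and Monitoring section, under known harms, participants are described as being in regular contact with the team, "with Structured Assessments every 3-weeks and regular facilitator calls during the DWM phase". If an undesirable reaction or significant symptoms come up, "then the trained assessor/facilitator will be able to triage the issue by either" giving referral information or escalating to the clinical supervisor.

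The Treatment of Subjects section fixes who has which contacts:
- **Active arm:** "participants will also receive five weekly calls from a trained facilitator", and "Participants in the Active Treatment condition will receive the 5-week DWM intervention from Weeks 1-5".
- **Both arms:** "Regardless of condition, all participants will complete Structured Assessments every 3 weeks".
- **Waitlist:** "Participants in the Waitlist Control condition will participate in repeated assessments (mid-treatment, post-treatment and follow-up assessments) over a 9-week waitlist period". No facilitator calls are described for this arm.

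The Measurement Instruments table schedules the K10, PCL-6, SIDAS, PSYCHLOPS, WHO-5, physical health and other scales at Structured Assessment 1 and at Structured Assessments 2-4. It has no adverse-event row. The adverse life events checklist is given at baseline only.

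Recorded events go into a safety monitoring register. A copy goes to the sponsor's delegate each year with an "Analysis of the trial intervention(s) and its implications for participants considering all available safety data". The Statistics section adds that "Interim analyses will be considered in case safety issues are (suspected to be) violated".

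**The concern.** Section 11 sets out how an event is classified and routed once someone has raised it. It does not say how events are asked about. What reaches the register therefore depends on when a participant next speaks to an assessor or facilitator, and that differs by arm while DWM is being delivered.

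If true event rates were the same in both arms, minor events could be recorded more often under DWM in weeks 1-5, with the difference vanishing once the calls end. On paper that resembles a treatment harm that resolves. In the other direction, a true excess of events among people waiting nine weeks could go partly unseen. An event that nobody asked about in the waitlist arm cannot be recovered at the analysis stage.

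**Working it through.** The protocol gives no figure to reproduce here. The check counts scheduled contacts and then asks what they imply if true event rates are equal.

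**Contacts after baseline.** Assessments every 3 weeks fall at weeks 3, 6 and 9 in both arms (Treatment of Subjects). Calls fall in weeks 1-5 in DWM only.

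| Period | DWM | Waitlist |
| --- | --- | --- |
| Weeks 1-5 | 5 calls + 1 assessment = 6 | 1 assessment |
| Weeks 6-9 | 2 assessments | 2 assessments |
| Total | 8 | 3 |

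**Coverage model.** Assumptions: events are equally likely on each of days 1-63 in both arms; an event is recorded if a contact falls on that day or within the r-day window starting that day; every contact elicits every event still remembered. Assessments are on days 21, 42 and 63. The call days are not stated, so two layouts are used: days 1, 8, 15, 22, 29 or days 8, 15, 22, 29, 36. The protocol gives no recall window, so r is varied.

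Coverage = covered days / days in the period. Ratio = DWM coverage / waitlist coverage.

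| r | Period | DWM days covered | Waitlist days covered | Ratio |
| --- | --- | --- | --- | --- |
| 7 | days 1-35 | 29 to 34 of 35 | 7 of 35 | 4.14 to 4.86 |
| 7 | days 36-63 | 14 of 28 | 14 of 28 | 1.00 |
| 7 | days 1-63 | 43 to 48 of 63 | 21 of 63 | 2.05 to 2.29 |
| 14 | days 1-35 | 35 of 35 | 21 of 35 | 1.67 |
| 14 | days 36-63 | 21 of 28 | 21 of 28 | 1.00 |
| 14 | days 1-63 | 56 of 63 | 42 of 63 | 1.33 |
| 21 | days 1-63 | 63 of 63 | 63 of 63 | 1.00 |

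**Incomplete reporting.** Suppose each contact elicits a remembered event with probability 0.5 and recall lasts 3 weeks. Calls are now placed at the ends of weeks 1-5. Detection is 1 - 0.5^k, where k is the number of contacts in the 3 weeks after the event.
- Waitlist: k = 1 throughout, so detection is 0.50.
- DWM: k = 4 in each of the first three weeks, 3 in the fourth, 2 in the fifth and 1 in the last four. Mean detection = (3 × 0.9375 + 0.875 + 0.75 + 4 × 0.50) / 9 = 6.4375 / 9 = 0.72.
- Ratio = 1.43. At a reporting probability of 0.25 it is 1.81.

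Equal detection therefore needs both recall across the gap between assessments and complete reporting.

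**EMA blocks.** Both arms have two 7-day EMA blocks, and participants who miss 2 or more of the 5 daily surveys are contacted. The items cover emotions, regulation strategies and stressors, so they are left out of the counts above. As an extreme case, suppose EMA caught every event on days 1-7 and 43-49. At r = 7 the waitlist then covers 35 of 63 days and DWM 50 to 56, a ratio of 1.43 to 1.60. The imbalance shrinks but stays.

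**Allocation.** Randomisation is 2:1, so raw counts would be about twice as high under DWM from arm size alone. The ratios above are per participant.

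**The case against.** The strongest reply is that the protocol plans no comparison of event counts by arm or by period. Each event is assessed individually for seriousness, causality and expectedness, and the interim-analysis sentence sets no count-based trigger. How events are tabulated by arm may properly be left to the SAP. All of this stands. A reader might infer that the annual report or an interim analysis would act on an artefact, but the document does not support that. What remains is a matter of data collection: an SAP cannot compare events that were never elicited.

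A reader might also infer that events must be higher under DWM by construction. They need not be. The assessments run in both arms to week 9, full recall over 21 days with complete reporting gives a ratio of 1.00, and a real benefit of DWM could offset the extra detection. Nor is SIDAS the only safety-relevant measure taken equally: the K10, PCL-6, WHO-5 and physical-health items are too. These will show worsening symptoms evenly, but they are scores and do not report events.

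The recall windows are assumptions. Deaths, hospitalisations and permanent impairment are unlikely to be forgotten within three weeks, so the bias concerns mainly non-serious events. The register template and report form are only linked, and the safety flow chart is not reproduced, so it cannot be said that the register lacks a source field.

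**Conclusion.** The point holds as a detection imbalance, and the remedy is cheap. Scheduled contact with an assessor or facilitator is about 6 against 1 in weeks 1-5 and equal afterwards, and neither the Measurement Instruments table nor Section 11 states an adverse-event question common to both arms. Any comparison of recorded events by arm or period may be biased, chiefly for non-serious events.

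Under equal true rates and complete reporting, the nine-week ratio per participant runs from 1.00 (21-day recall) through 1.33 (14 days) to 2.05 to 2.29 (7 days). Incomplete reporting raises it; any detection through EMA lowers it. These figures depend on the assumed recall window and call days. They show direction and plausible size and do not forecast what the register will contain.

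**What to change.** - Add one standard question on untoward events since the last assessment at Structured Assessments 2, 3 and 4, in both arms. Make it self-completed so that answers do not reveal allocation to the blinded assessor; the protocol already uses self-report for the contamination and perceived-benefit items. Ask for all events, including any already mentioned to a facilitator, so that DWM participants do not leave them out.
- Flag in the register how each event came to light.
- State in Section 11 that any comparison between arms or periods uses events from this question, as per-participant rates because of the 2:1 allocation, with call-detected events listed separately.
- Keep events from every source in the safety review, the annual report and any decision on an interim analysis. Leaving call-detected events out of these would conflict with the annual report's own requirement to consider all available safety data.

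With three post-baseline assessments in each arm, scheduled ascertainment for comparisons is then equal by design.

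The cost is one item at three assessments already planned, a source field and a few sentences in Section 11. Three-week recall may miss minor events.
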